#### Follow-up

All patients will return for follow-up examinations every 3 months for two years and then every 6 months for the remainder of the study period. At each visit the entire oral mucosa will be examined under WL, with surgery sites photographed. The presence of lesions will be noted on lesion tracking sheets along with lesion size and location. Updated clinical information, digital images and data fields from the quality of life questionnaires will be uploaded to the database by the SC.

Decision to biopsy will depend on the clinical judgment of the surgeon, based on suspicion of a recurrence. If there is no significant clinical change, a biopsy will be taken at the surgery site at 2-year post surgery. A repeat CT scan is warranted if there is clinical suspicion of regional or distant diseases. If there is no clinical indication, Neck CT scan and a chest X-ray will be arranged at 2-year post surgery follow-up.

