## Methods/design

### Study design

The COOLS trial is a multicentre, double blind, randomized controlled study, comparing FV- guided surgery (experimental arm) to conventional white light (WL)-guided surgery (control arm). See Figure 1 for the schema of the study.

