##### a. If this is a FV-guided surgery (experimental arm)

With the operating room (OR) lights off, the FVS will use the VELscope Vx to examine the lesion and outline the FV change using a green Sharpie pen. After the FV positive boundary is outlined, images (***Image 2***) are taken in the dark to demonstrate the distance between FVL and clinical outline.

With the OR light back on, the FVS will measure the distance from FV boundary to the clinical boundary in 4 directions, and record this on the surgical tracking sheet. The site surgeon will outline a 10 mm surgical boundary around the clinically visible tumor and FV boundaries, whichever is wider. The FVS will take images (*Image 3*) under both FV and WL and record if there is any anatomical restriction for the placement of the standardized surgical boundary.

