##### b. If this is a WL- guided surgery (control arm)

With the light off, the FVS will use the VELscope VX to examine the lesion and draw an outline on top of the surgeon's clinical boundary using a green Sharpie pen. After this step, the FVS will take another set of images (*Image 2*). In this case, the 2 outlines will be identical and this will be recorded on the surgical tracking sheet. The surgeon will outline a 10 mm surgical boundary around the clinical/FV boundary. The FVS will take images (*Image 3*) under both FV and WL and record if there is any anatomical restriction for the placement of the standardized surgical boundary.

The operating surgeon will remain outside the OR while the FVS marks the boundaries. Although it is unlikely the surgeon will remain blinded once the two markings are made, any deviation from the marked boundary will be recorded to allow assessment of deviation from the protocol.

Blood samples (5 ml in SST and 12 ml in EDTA tubes) will be collected at this time prior to the surgery. The tumor will then be resected and oriented using a suture for the anterior or right orientation. This will be indicated on the routine pathology requisition form to help the SP to orient the resected tissue. The specimen will be wrapped in a piece of cold saline gauze and kept on ice during transfer to the Pathology Department for processing.

The Site Pathologist (SP) will either use the tracking sheet or a print-out of the digital image of the excised tissue to record the tissue blocking. One-week after the diagnosis has been determined all the H&E sections will be sent to the Central Histology Review committee for histological review. If there is disagreement on the assessment between the site pathologist and the review committee, a teleconference will be arranged in order to discuss and achieve consensus. The site coordinator will upload all images, surgical and pathological CRFs and key information from pathology reports into the study database.

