### Randomization

Stratified randomization will be employed. Two stratification factors will be applied: 1) institution and 2) histological grade of the primary lesion (severe dysplasia and carcinoma *in situ *or invasive squamous cell carcinoma).

A randomization program has been written specifically for this trial ([name]). According to the information collected, the central database manager under the supervision of the study biostatistician ([name]) will perform the randomization. Within each stratum, the minimization algorithm will be used to achieve balanced randomization with respect to other prognostic factors, including surgeon, gender, age, smoking history, and lesion anatomical sites. [20]

The randomization will be done 1 - 2 days prior to surgery. Only the FVS will be notified of the result. The patient, research staff, operating surgeon, and the pathologist are not aware of the assignment. The allocation list will be held by the study database manager; this individual is not involved in patient care or recruitment. The allocation will only be revealed in the event of an emergency medical situation.

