## Outcome evaluation

### Primary endpoint

A composite endpoint will be used for outcome evaluation. The components are 1) local recurrence defined as a recurrence at or within 1 cm of the previous surgery site, with the same or higher grade histology compared to the initial diagnosis or 2) further treatment due to the presence of severe dysplasia or higher degree of change at follow-up. This is consistent with the current practice at all participating sites that only high-grade lesions (i.e. ≥ severe dysplasia) require further treatment. The endpoint will be evaluated and adjudicated by the Centre Pathology Review Committee (chaired by [name]) of which members are blinded to the treatment assignment.

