For clinical images and the use of VELscope, all FV operators (FVS and SS) will need to pass a 2-step control process. Step 1: as part of the training process, two sets of 8 images will be provided to the site surgeons and FVS, as a first step in calibrating their judgment on clinically visible tumor boundaries and FV positive (FV loss) boundaries. The criteria for passing the step is that both clinically visible tumor boundaries and FV boundaries need to be within ± 5 mm of those drawn by the experienced FV operators from the British Columbia (BC) site. Step 2 **: **to be certified, all FV operators require hands-on experience in outlining the tumor and FV boundaries on 2 real patients. The same criteria will be used to assess this activity, with a requirement that both clinically visible tumor and FV boundaries be within ± 5 mm of those drawn by the experienced FV operators from BC site. This time, the BC specialists will draw on the images received from the study sites. This can be used to review the entire operation from new patient assessment to the completion of surgery (see Key Steps above) to ensure the high-quality operation.

After passing this 2-step control process, a site will be ready to recruit the first patient to the study. The PI ([name]) will review the first 10 patients from each site to ensure the quality of images is maintained and that mapping of clinical and fluorescence boundaries proceeds as per initial training and to provide suggestions to the site team members for any problems experienced during these activities. Subsequently, about 5% random samples from each site will be selected from time to time to check for the accuracy of boundary drawings. This can also mitigate 'margin creep' over time.

One risk is the potential contamination of endpoint by the surgeon, i.e., margin creep (expanding margins) in the control arm. We are requiring that both the FV and white light margins be justified just prior to surgery in the operating room with the presence of both surgeon and an independent party for FV assessment. In this fashion, the surgical margin will be placed in a consented and unbiased fashion. In order to keep the study double blinded and avoid potential bias, the FVS will be a different person from the SS. The periodic review of sites by central management team will also mitigate this problem.

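### The trial is labelled double blind, but the operating surgeon will probably know the arm, and a surgeon's judgment triggers every biopsy outside the one scheduled at 2 years

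*Protocol article*

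**What the plan says.** Study design states: "The COOLS trial is a multicentre, double blind, randomized controlled study". The Abstract uses the same label. Under Randomization, only the FV specialist is told the result, and "The patient, research staff, operating surgeon, and the pathologist are not aware of the assignment". Fidelity of the intervention gives a safeguard: "In order to keep the study double blinded and avoid potential bias, the FVS will be a different person from the SS".

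The two surgical procedures describe what the surgeon sees after the specialist has marked the lesion. In the control arm, "In this case, the 2 outlines will be identical and this will be recorded on the surgical tracking sheet". In the experimental arm, "The site surgeon will outline a 10 mm surgical boundary around the clinically visible tumor and FV boundaries, whichever is wider". The control-arm section then concedes: "Although it is unlikely the surgeon will remain blinded once the two markings are made". Its stated response is to record departures from the marked boundary.

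Follow-up says: "Decision to biopsy will depend on the clinical judgment of the surgeon, based on suspicion of a recurrence". It adds one biopsy of the surgery site at 2 years for patients without significant clinical change. Visits continue every 6 months after that, with no further scheduled biopsy described.

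The primary endpoint combines local recurrence of the same or higher grade with "2) further treatment due to the presence of severe dysplasia or higher degree of change at follow-up". A pathology review committee blinded to treatment adjudicates it and, according to the Discussion, works from the follow-up biopsies.

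**The concern.** The design does not deliver a property that the plan claims for it. The surgeon works from the marks, and the marks carry information about the arm: coinciding outlines in one arm, outlines that may differ in the other. Keeping the surgeon out of the room during marking does not remove that cue.

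The loss of blinding matters because histology defines the endpoint and somebody must first decide to take tissue. If that person knows the arm, lesions can be sought more or less readily in one arm than in the other. Blinded adjudication cannot see a biopsy that was never taken. The plan deals with the surgeon's knowledge only as a threat to the surgical margin (recorded deviations, margin creep), not to detection during follow-up.

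**Working it through.** **1. The statements side by side.** The Abstract, Study design and Fidelity sections claim double blinding, and Randomization names the operating surgeon as unaware. The control-arm procedure says this is unlikely to last beyond marking. Follow-up gives the biopsy decision to the surgeon, and no section assigns follow-up to an examiner unaware of allocation.

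**2. The plan's own sample size, for reference.** Inputs from Statistical design and analysis: 25% failure at 3 years on white light, exponential times, hazard ratio 0.5, 36-month accrual, minimum follow-up 2 years, two-sided α of 0.05, 80% power.
- Control hazard: λ = −ln(0.75)/3 = 0.0959 per year.
- Event probability with follow-up uniform on 2 to 5 years: P = 1 − (e^(−2λ) − e^(−5λ))/(3λ). This is 0.2826 for white light and, with λ/2, 0.1538 for FV; the mean is 0.218.
- Events needed (Schoenfeld): 4(1.960 + 0.842)²/(ln 0.5)² = 65.3, so 66; N = 66/0.2182 = 303.
- With 350 patients: 76 expected events and 85.7% power.

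The stated 350 for at least 80% power is therefore met, and nothing here changes it.

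**3. Share of events that no scheduled biopsy follows.**
- Probability of a control-arm event by year 2: 1 − e^(−2λ) = 0.1745.
- Share by year 2: 0.1745/0.2826 = 62%. Share after year 2: 38%.

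**4. Illustration of possible bias.** The true hazard ratio is 1, N = 350, and 10% or 20% of FV-arm lesions are missed when they arise. These fractions, and the choice of the FV arm, are assumptions; the documents contain neither.

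If detection is lower throughout and missed lesions are never found, the FV hazard is multiplied by 0.9 or 0.8:
- Factor 0.9: 94.7 events; z = √(94.7/4) × |ln 0.9| = 0.513; rejection = Φ(0.513 − 1.96) + Φ(−0.513 − 1.96) = 0.074 + 0.007 = 8.1%.
- Factor 0.8: 90.4 events; z = 1.061; rejection = 0.184 + 0.001 = 18.5%.

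The other two scenarios use a simulated log-rank test (20,000 runs each):

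| What happens to missed lesions | 10% missed | 20% missed |
|---|---|---|
| Arising before year 2: found at the 2-year biopsy; later ones lost | about 5.5–6% | 7–8% |
| Arising before year 2: delayed to the 2-year biopsy; none lost | about 5% | about 5% |
| Never found (formula above) | 8.1% | 18.5% |

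The first row was 5.4–5.6% and 7.3–8.0% across separate runs, which differed in whether detection was tied to the visit schedule. Deleting missed events patient by patient in the same simulation, instead of scaling the hazard, puts the last row slightly higher (about 9% and 21–23%). The ordering is unchanged.

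**The case against.** **The Randomization statement may describe only the time of assignment**, 1–2 days before surgery, with the later concession an open disclosure. That reading is possible for the sentence itself. It does not rescue the overall label, or the claim in Fidelity of the intervention that a separate specialist keeps the study double blinded.

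**Unblinding need not be universal.** The FV outline need not extend beyond the clinical one in every experimental-arm patient. This is fair, but the plan itself expects the blind to fail.

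**The surgeon in Follow-up is not called the operating surgeon.** True; that they are the same person is the natural reading, not a stated fact.

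**Both arms share visits, white-light examination, photographs and lesion tracking, and the 2-year biopsy does not need suspicion.** These are real safeguards, and the 2-year biopsy removes most of the illustrated inflation. Its reach is limited: it is a single biopsy of the surgery site, while local recurrence extends to 1 cm around it, and nothing comparable follows later.

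**Stronger readings to resist.**
- A reader might infer that the trial is biased towards FV with a type I error of 8% or 19%. Those figures require misses in the FV arm only, throughout follow-up and never recovered, which sets the 2-year biopsy aside.
- A reader might treat the further-treatment component as a second major route for bias. The Primary endpoint section reports that treating high-grade lesions, and only those, is current practice at all sites, and the component still requires severe dysplasia or worse. The live route is the biopsy decision.
- It is tempting to make that component purely histological and say that no events would be lost. This would not blind the biopsy decision. Adding the 1 cm limit, which the Primary endpoint section attaches to the first component only, could drop events.

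**Conclusion.** The point holds as a misdescription of blinding combined with an open route for differential ascertainment. The plan claims a blinded operating surgeon and concedes elsewhere that this is unlikely to last. It leaves whether and when to biopsy, apart from the 2-year biopsy, to a surgeon who is naturally read as the same person.

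The exposure is mainly in the 38% of expected control-arm events after year 2. That share rests on the plan's exponential, 25%-at-3-years assumption and uniform accrual. If the 2-year biopsy is done in nearly everyone and samples the lesion, the illustrated type I error is about 5% to 8%; where that fails, it moves towards the higher figures. Whether any bias exists, and in which direction, cannot be derived from the documents. This should be corrected, but it does not show that the primary comparison is invalid.

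**What to change.** 1. **Reconcile the blinding statements** in the Abstract, Study design, the control-arm procedure, Randomization and Fidelity of the intervention. Describe the trial as blinded for the patient, the pathology review committee and the biostatistician (who sees masked treatment labels), with the operating surgeon not reliably blinded after marking.
2. **Prespecify a sensitivity analysis** of the primary endpoint on event status through the 2-year biopsy. Minimum follow-up is 2 years, so every retained patient can contribute. Report unscheduled biopsies per patient-year by arm, so that any difference in ascertainment is visible.

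Cost: wording, one extra analysis and one table, all from data already planned for collection. The blinding description becomes less favourable. The extra analysis is also weaker: by year 2 the event probabilities are 0.1745 and, at hazard ratio 0.5, 1 − e^(−λ) = 0.0914. That gives 350 × 0.133 = 47 events and about 66% power, against 86% for the full follow-up. These steps expose and bound the problem; they do not blind the biopsy decision.

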### Randomization

Stratified randomization will be employed. Two stratification factors will be applied: 1) institution and 2) histological grade of the primary lesion (severe dysplasia and carcinoma *in situ *or invasive squamous cell carcinoma).

A randomization program has been written specifically for this trial ([name]). According to the information collected, the central database manager under the supervision of the study biostatistician ([name]) will perform the randomization. Within each stratum, the minimization algorithm will be used to achieve balanced randomization with respect to other prognostic factors, including surgeon, gender, age, smoking history, and lesion anatomical sites. [20]

The randomization will be done 1 - 2 days prior to surgery. Only the FVS will be notified of the result. The patient, research staff, operating surgeon, and the pathologist are not aware of the assignment. The allocation list will be held by the study database manager; this individual is not involved in patient care or recruitment. The allocation will only be revealed in the event of an emergency medical situation.

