### Inclusion Criteria

Patients with disease localization at oral anatomical sites that can be visualized using both white light and fluorescence visualization device (this includes ICD-10 site codes: C02.0-C06.9); patients with a clinical diagnosis of N0 or N1 as confirmed by CT scan, with the latter undergoing neck dissection; or patients with resectable locally recurrent disease diagnosed with severe dysplasia or higher grade, provided that they are at least 6 months post-treatment (this time frame will allow resolution of artefacts produced by treatment that could impact on tumor or lesion visualization).

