### Sample size

Assuming the survival curves follow exponential distributions, a 25% failure rate at 3 years in the WL arm and a hazard ratio of 0.5 (i.e. ~12.5% failure rate in the FV arm), a 36-month accrual period, a minimum of 2 years of follow-up, with an overall two-sided α = 0.05, a total sample size of 350 patients is required to achieve at least 80% power using the stratified log-rank test. Assuming 10% of patients may be lost to follow-up we will randomize 400 patients.

Two interim analyses for efficacy are planned (at one-third and two-thirds of predicted outcomes) with a final analysis at the end of Year 5. A Lan-Demets spending function with O' Brien-Fleming type stopping boundaries will be employed.

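### Locally recurrent lesions are eligible and the endpoint is local recurrence, but recurrent status at entry is not named among the stratification or minimisation factors

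*Protocol article*

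**What the plan says.** Inclusion Criteria (protocol article) admits "patients with resectable locally recurrent disease diagnosed with severe dysplasia or higher grade, provided that they are at least 6 months post-treatment". Primary endpoint makes local recurrence of the same or higher grade, close to the earlier resection, the first component of the composite. The second component is further treatment for severe dysplasia or worse.

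Randomization fixes two strata, institution and histological grade. Within each stratum it minimises on "other prognostic factors, including surgeon, gender, age, smoking history, and lesion anatomical sites". Recurrent status appears in neither list.

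The only test named is in Sample size, under Statistical design and analysis: "a total sample size of 350 patients is required to achieve at least 80% power using the stratified log-rank test". The strata of that test are not listed. The article does not say whether a covariate-adjusted analysis is planned.

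**The concern.** A lesion that has already come back after treatment is a plausible marker of higher risk of coming back again. The Background section supports this, because it attributes local recurrence to occult field change beyond the visible tumour. Recurrent status must also be known at entry, since a six-month rule applies to these patients. Gender and smoking are named for balancing, yet prior local failure is not.

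Two things are at stake. The arms may differ by chance in the share of previously failed lesions, in a trial expecting only about 76 events. An analysis that ignores a strong baseline predictor also gives up some power. Allocation factors cannot be added by an SAP once patients are randomised, so the balancing part belongs in the protocol.

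**Working it through.** **Inputs from Sample size:** "a 25% failure rate at 3 years in the WL arm and a hazard ratio of 0.5"; "a 36-month accrual period, a minimum of 2 years of follow-up"; "with an overall two-sided α = 0.05"; 350 evaluable patients. From Randomization and the list of centres: 9 institutions × 2 histology groups = 18 strata. **Assumed, because the documents are silent:** 15-30% of lesions recurrent, hazard ratio H = 2-3 for recurrent against first lesions, and moderate effects of the five minimised factors.

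**1. The plan's own figure.**
- Yearly hazards: WL −ln(0.75)/3 = 0.0959; FV half of that, 0.0479.
- Event probability with uniform 3-year accrual and 2 further years: 1 − (e^(−2λ) − e^(−5λ))/(3λ) = 0.283 (WL) and 0.154 (FV), mean 0.218.
- Events for 80% power: Schoenfeld 4(1.96 + 0.84)²/(ln 0.5)² = 66; Freedman (1.96 + 0.84)² × (1.5/0.5)² = 71.
- Patients: 66/0.218 = 303, or 71/0.218 = 326.
- At 350 patients: 350 × 0.218 ≈ 76 events, power 85.7% (Schoenfeld) or 83.0% (Freedman).
- Loss to follow-up: 350/0.9 = 389, rounded up to 400.

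The statement of at least 80% power therefore holds. If the log-rank uses the randomisation strata, 76/18 is about 4 events per stratum.

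**2. Chance imbalance.** With 175 per arm, the SD of the difference in recurrent share is √(p(1−p) × 2/175).
- p = 0.15: SD 0.038, 95% range ±7.5 points.
- p = 0.30: SD 0.049, 95% range ±9.6 points.

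Simulating the planned minimisation within 18 strata gave 95th percentiles of 7-8 and about 10 points. With recurrent status added to the minimisation they fell to about 6 and 7 points.

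**3. Effect on the hazard ratio.** For imbalance d, the average baseline hazards differ by the factor (1 + (p + d/2)(H−1))/(1 + (p − d/2)(H−1)).
- p = 0.15, d = 0.07, H = 2: 1.185/1.115 = 1.063, so 0.50 becomes 0.53 or 0.47.
- p = 0.30, d = 0.10, H = 3: 1.70/1.50 = 1.133, so 0.50 becomes 0.57 or 0.44.

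For scale, the standard error of the log hazard ratio is about 2/√76 = 0.23. The shifts, ln 1.063 = 0.06 and ln 1.133 = 0.12, are about a quarter and a half of one standard error.

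**4. Power by method** (simulation, 350 patients, HR 0.5, no interim looks, 600 runs each, standard error about 1.5-2 points):

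| Recurrent share / H | Log-rank, 18 strata | Log-rank, 36 strata (recurrence added) | Cox, stratified by histology, adjusted for recurrence and the five factors |
|---|---|---|---|
| 15% / 2 | 0.82 | 0.77 | 0.84 |
| 15% / 3 | 0.78 | 0.73 | 0.85 |
| 30% / 3 | 0.77 | 0.73 | 0.85 |

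The third row also assumes stronger effects of the five factors. Under the null, rejection rates were 0.037-0.047 for the 18-stratum log-rank and 0.045-0.055 for the Cox model.

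Further runs (20% recurrent, H = 2-3, 500 per scenario) gave 0.79-0.81 for the 18-stratum log-rank, 0.83-0.85 for Cox stratified by histology, and 0.82-0.84 for Cox keeping all 18 strata. Type I error there was about 6-7% for both methods; with a simulation error of about 1 point, this gives no reason to prefer either method on that ground.

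**The case against.** Several stronger readings are tempting, and the document does not support them.

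- **That the primary test leaves out recurrent status and the five minimised factors.** The log-rank is named only in a sample-size sentence, and its strata are not given. Equating them with the two randomisation strata is likely but inferred. Covariate adjustment is commonly left to the SAP, which is not shown, so its absence cannot be claimed. This objection stands.
- **That recurrent status is certainly unbalanced.** The word *including* leaves the minimisation list open, and the article is condensed. What can be said is that the factor is not named. This stands too.
- **That the imbalance is bias.** It is random, can fall either way, and is already allowed for in the test's error rate. The shifts above are 95th-percentile cases.
- **That the trial is underpowered.** Step 1 contradicts this on the plan's own assumptions. The simulated values of 0.77-0.78 arise only under added assumptions about prognosis.

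It is also fair to say that part of the gain from the Cox model comes from using fewer strata, not from adjustment. The runs that keep all 18 strata show a gain about one point smaller.

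What survives is narrow: a baseline fact tied closely to the endpoint, already needed for eligibility, is missing from the named balancing factors.

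**Conclusion.** The point holds as a modest design gap. Recurrent lesions are eligible, the endpoint is local recurrence, and recurrent status is not among the named stratification or minimisation factors. On assumed shares of 15-30% and hazards 2-3 times higher, the 95th-percentile imbalance is about 7-10 points. The hazard ratio then moves from 0.50 to 0.47-0.53 (7 points, H = 2) or 0.44-0.57 (10 points, H = 3). Adjustment is worth roughly 2-8 points of power. If recurrent lesions are rarer or less prognostic than assumed, the effect is smaller. A reader should not infer an invalid test, a wrong sample size or a missing adjusted analysis.

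**What to change.** 1. Add recurrent lesion at entry (yes/no) to the minimisation factors for the remaining patients, or state that the program already uses it. The Discussion reports 69 of 400 enrolled at the time of writing, leaving 331.
2. Name the strata of the log-rank test.
3. Pre-specify, beside the stratified log-rank on which the trial was sized, a Cox estimate of the treatment effect. Stratify it by histology, account for institution (for example by keeping it as a stratum), and adjust for recurrent status, age, smoking, gender and anatomical site. Either include surgeon or justify leaving it out.
4. Do not add recurrent status as a further log-rank stratum. With about 76 events over 18 strata, if those are the strata used, doubling them cost 4-5 points of power in the simulation.

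The cost is a small change to the randomisation program, some SAP wording and a little more analysis. The factors are baseline facts already needed for eligibility or allocation. The first 69 patients will not have been balanced on the new factor, and the adjusted estimate covers that.
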